### Analysis of Quantitative Data

Analyses will be conducted according to the intention-to-treat principle, and the Bonferroni correction will be used to control for multiple testing. The primary outcome is to assess difference in vaccination status. Chi-square test will first be used to compare the groups’ percentage. Multivariable logistic regression analyses will be conducted to adjust for confounders. As our randomization unit is cluster-based rather than individual-based, generalized linear mixed effects models or generalized estimating equations models will be employed to account for within-cluster correlation, and hierarchal models will be used. The statistical model for the primary and secondary analyses will be developed as explanatory variables. As secondary analyses of the primary outcome, time-to-immunization curves will be constructed using the Kaplan-Meier method and Cox regression for multivariate analysis.

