### Randomized Clinical Trial

The study design is a cluster randomized clinical trial including 4 intervention and 1 control arm (Table 2).

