#### Sample Size Calculations

Assumptions used for calculating sample size are as follows: increase in coverage rate from 30% to 40%, having a power of 80% with an alpha error at .05. The sample size per arm would be 615 per arm or 3075 for all 5 arms. Adding a 10% dropout will make it 677 per arm or 3385 recruitment for all 5 study arms. The ICC is taken as .05, with an estimate of 15 NB per cluster (see Table 3).

**Table 2 table2:** Cluster randomized clinical trial.

Study arm	Automated SMS^a^ text and phone calls			
	1-way SMS text	2-way SMS text	1-way phone calls	2-way phone calls
1	X^b^	—^c^	—	—
2	—	—	X	—
3	—	X	—	—
4	—	—	—	X
5	—	—	—	—

^a^SMS: short message service.

^b^Applicable.

^c^Not applicable.

**Table 3 table3:** Sample size calculation. Having a difference of 10% and the sample size given (ie, 1230 is 2 groups, 1:1) in our study, we have 5 groups (615x5)+10% dropout=3385.

Serial #	Interclass correlation	Range of cluster size					
		Cluster size of 15		Cluster size of 20		Cluster size of 30	
		Clusters, n	Total birth required, n	Clusters, n	Total birth required, n	Clusters, n	Total birth required, n
1	0.01	54	810	44	880	32	960
2	0.05	82	1230	70	1400	58	1740
3	0.09	108	1620	98	1960	86	2580
4	0.1	114	1710	104	2080	94	2820
5	0.13	134	2010	124	2480	114	3420
6	0.15	148	2220	138	2760	128	3840
7	0.2	180	2700	172	3440	162	4860
8	0.21	188	2820	178	3560	168	5040
9	0.25	214	3210	206	4120	196	5880
10	0.3	248	3720	238	4760	230	6900
11	0.35	280	4200	272	5440	264	7920
12	0.37	294	4410	286	5720	278	8340
13	0.4	314	4710	306	6120	300	9000
14	0.45	346	5190	340	6800	334	10,020
15	0.5	380	5700	374	7480	368	11,040

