### Statistical Analysis

Analyses will be conducted according to the intention-to-treat principle. When the information cannot be gathered, the vaccine status of the child will be *failure* (conservative approach). Missing the vaccine EPI card to verify vaccine status at home will lead to a deeper investigation in the family and also the vaccine clinic. From previous experience, we expect this process to be successful in identifying the outcome of over 95% (95/100) of the children who remain in the study at 20 weeks. Families that have left the study for any reason (moving, withdrawal, child death) will be interviewed (if possible) and the information gathered used for the outcome classification. If the information is not clear or incomplete, the child’s status regarding vaccination will be *failure*.

The main analyses will be comparing our 4 study intervention arms against the control, and with each other. For the purposes of our study, we will compare each of the 4 interventions with each other and with the control arm. For example, 1-way versus 2 SMS, reminder versus educational SMS, 1-way reminders SMS versus control, 1-way educational SMS versus control, 2-way reminders SMS versus control, 2-way educational SMS versus control, 2-way education versus 1-way reminder, and 2-way reminder versus 1-way educational.

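### Bonferroni is valid here but needlessly strict for the tests; Holm's step-down procedure keeps the same family-wise error control and gains a little power at almost no cost

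*Protocol article*

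**What the plan says.** The section Analysis of Quantitative Data fixes the multiplicity method: "the Bonferroni correction will be used to control for multiple testing". It names no step-down variant, number of tests or family. The same section plans mixed or GEE models to allow for clustering.

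The section Randomized Clinical Trial describes a "cluster randomized clinical trial including 4 intervention and 1 control arm". Under Statistical Analysis the article adds that "we will compare each of the 4 interventions with each other and with the control arm". Five arms give 5 × 4 / 2 = 10 pairs: 4 against control and 6 between interventions. The examples that follow include reminder versus educational messages, which are not randomized arms. The Outcomes section lists several primary outcomes, among them SMS versus calls.

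Sample Size Calculations assumes an "increase in coverage rate from 30% to 40%, having a power of 80% with an alpha error at .05". It also states: "The ICC is taken as .05, with an estimate of 15 NB per cluster".

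**The concern.** Bonferroni named without qualification is the single-step method. Each of m contrasts is tested at alpha/m, however many others have already been rejected. Once some null hypotheses are rejected, fewer can still be true, and a step-down procedure relaxes the threshold accordingly without losing family-wise control. The all-pairs family has a further feature: the equalities are logically linked. If one pair of arms differs, at most 6 of the other 9 equalities can hold together (four arms equal, one different).

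What is at stake is power to confirm arms that work. The Study Hypothesis section expects both SMS and calls to improve uptake, so more than one true difference is the planned setting. The Result section reports enrolment as complete, so the sample size is settled, whereas the testing procedure can still be changed.

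The article itself chose the method, so this is not a matter of detail left to an analysis plan that is not shown.

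**Working it through.** **1. Reproduce the planned size.** Inputs from Sample Size Calculations: 30% vs 40%, power 80%, alpha .05 (two-sided assumed), ICC .05, 15 per cluster.

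- Individual randomization, no continuity correction: n = [1.96·√(2·0.35·0.65) + 0.8416·√(0.21 + 0.24)]² / 0.10² = 356 per arm.
- Design effect: 1 + 14 × 0.05 = 1.70; 356 × 1.70 = 605.2, which rounds up to 41 clusters of 15 = 615 per arm, or 82 clusters and 1230 births for two arms, as in Table 3.
- With dropout: 615 × 1.10 = 676.5, rounded to 677; × 5 = 3385.

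This matches "The sample size per arm would be 615 per arm or 3075 for all 5 arms" and "Adding a 10% dropout will make it 677 per arm or 3385 recruitment for all 5 study arms". The plan's figure therefore rests on one pairwise test at unadjusted alpha .05.

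**2. Power of one contrast at the Bonferroni level.** Effective n = 615/1.70 = 361.8 per arm. Pooled SE = √(0.455/361.8) = 0.03546; unpooled SE = √(0.45/361.8) = 0.03527. Power = Φ[(0.10 − z × 0.03546)/0.03527]:

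- alpha .05 (z = 1.960): 80.6%
- alpha .05/4 = .0125 (z = 2.498): 62.7%
- alpha .05/10 = .005 (z = 2.807): 50.5%

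**3. Why Holm cannot do worse.** Order the 10 p-values and stop at the first that fails. The divisors of alpha are:

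- Bonferroni: 10 at every step
- Holm: 10, 9, 8, 7, 6, 5, 4, 3, 2, 1
- Shaffer, five arms, all pairs: 10, 6, 6, 6, 6, 4, 4, 3, 2, 1

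The Shaffer row comes from the numbers of equalities that can be true together among five arms: 10, 6, 4, 3, 2, 1 or 0. No step-down divisor exceeds 10, so any p-value at or below alpha/10 is rejected by all three.

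**4. Size of the gain.** Simulation: 200,000 sets of five independent, normally distributed arm estimates with variance p(1−p) × 1.70/615, two-sided pooled z tests, control 30%, all four interventions 40%.

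| Family | Measure | Bonferroni | Holm | Shaffer |
|---|---|---|---|---|
| 10 pairs | Average power per control contrast | 50.6% | 52.8% | 55.8% |
| 10 pairs | All four confirmed | 20.6% | 24.5% | 26.5% |
| 10 pairs | At least one true difference found | 80.6% | 80.6% | 80.6% |
| 10 pairs | Family-wise error | 2.7% | 3.3% | 4.2% |
| 4 control contrasts | Average power per contrast | 62.9% | 71.9% | n/a |
| 4 control contrasts | All four confirmed | 32.4% | 53.9% | n/a |

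A second simulation of the same setting gave 51.2/53.5/56.4% per contrast and 19.9/24.0/26.0% for all four. Under the global null the family-wise error was about 4.1% (10 pairs, all three methods) and 4.4% (4 contrasts), the highest value in any scenario.

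**5. Other effect patterns, 10 pairs (Bonferroni/Holm/Shaffer).**

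- Two arms effective, average over the true differences: 50.7/55.0/57.3%.
- One arm effective, likewise: 50.6/52.9/55.8%.
- Unequal effects (33, 33, 36 and 40%), best arm against control: 51.2/52.0/53.7%.

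**The case against.** The strongest reply is that nothing is wrong: Bonferroni is standard and controls the family-wise error under any dependence, so preferring another method is a matter of efficiency. That stands, and it sets the weight of the point. A reader might infer that the planned correction fails to protect the type I error; it does not fail.

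A second reply is that Bonferroni does give something in return, and this also stands. Its simultaneous confidence intervals match its tests. It also bounds the expected number of false rejections: with 10 pairs under the global null this was .050 for Bonferroni, .052 for Holm and .059 for Shaffer; with four effective arms it was .031, .040 and .050. The extra power comes from using slack in the family-wise error, which stays below 5%.

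Third, it is tempting to quote the larger gain, from 32% to about 54% for confirming all four arms. That figure needs a family of only the 4 control contrasts, and the Statistical Analysis section plans comparisons between interventions as well.

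Fourth, Shaffer's divisors hold only for exactly the 10 arm pairs on one outcome. The pooled SMS-versus-calls contrast, the reminder/educational contrasts and the several primary outcomes fall outside that structure. Holm needs no such structure and works for any family once it is defined.

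Fifth, it might be inferred that step-down testing gains most here because all four arms are expected to work. For all pairs, the simulations do not show this: one effective arm gives the same gain as four, two give more, and with unequal effects Holm adds less than 1 point for the best arm.

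None of these replies is a reason to prefer single-step Bonferroni for the tests themselves.

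**Conclusion.** The point holds as a cheap efficiency improvement, not as an error. For the all-pairs family the gain per control contrast is about 2 points with Holm and 5 with Shaffer, and the chance of confirming all four arms rises by 4 to 6 points from about 20%. The chance of at least one rejection is essentially unchanged. The gain from 63% to 72% per contrast would apply only if the confirmatory family were limited to the 4 control contrasts.

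A reader might infer that the change repairs the trial's power. It does not: power per contrast stays well below 80%, because the sample size was computed at unadjusted alpha. At alpha .005 about 1035 per arm before dropout would be needed, and at .0125 about 870, against 615 planned. That is a separate and larger matter.

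The figures assume two-sided tests, 615 analysed per arm, ICC .05, 15 per cluster, a normal approximation and, for the headline values, a common 40% in all four intervention arms.

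**What to change.** Before outcomes are analysed by arm, list the confirmatory contrasts and outcomes that form the family. Then replace the Bonferroni correction with the Holm step-down procedure at family-wise alpha .05, applied to the p-values of the cluster-aware model (the planned mixed or GEE model), not to those of the plain chi-square tests. Allow Shaffer's modification only if the family is exactly the 10 arm pairs on one outcome.

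The cost is a sentence or two and no change to the data. The one drawback is that simple simultaneous confidence intervals matching the step-down tests are not available. Report Bonferroni-width intervals alongside and say that they are conservative, since an interval may then include no difference where the Holm test rejects.

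### An ordinary chi-square test is named first for the primary outcome of a cluster-randomised trial, and the text does not say that the GLMM or GEE, rather than this test, supplies the p-values

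*Protocol article*

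**What the plan says.** The relevant text is one paragraph of the Protocol article, Analysis of Quantitative Data. It first sets intention-to-treat and a Bonferroni correction, without giving the number of tests. Four statements follow, in this order:

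1. The outcome and the first test: "The primary outcome is to assess difference in vaccination status. Chi-square test will first be used to compare the" groups' percentages.
2. A regression step: "Multivariable logistic regression analyses will be conducted to adjust for confounders".
3. The design feature: "As our randomization unit is cluster-based rather than individual-based". For this reason, generalised linear mixed models or generalised estimating equations are to account for within-cluster correlation, and hierarchical models are also to be used.
4. Kaplan-Meier curves and Cox regression, as secondary analyses of the primary outcome.

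The chi-square test is not labelled descriptive or preliminary, and no sentence says which analysis the Bonferroni-corrected p-values come from. The section Statistical Analysis makes the comparisons of the four intervention arms with control and with each other the main analyses.

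The section Sample Size Calculations does allow for clustering: "The ICC is taken as .05, with an estimate of 15 NB per cluster".

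**The concern.** The chi-square test computes its variance as if every child were an independent observation. When clusters are randomised and children in a cluster resemble each other, the true variance of a difference between arms is larger by the design effect. The test statistic is then too large and the p-value too small. The sample size and the first-named test therefore rest on incompatible variances: 1.70 times the independent variance in one, 1.00 times in the other.

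Following the paragraph as written produces a chi-square p-value for the primary outcome beside one from a cluster-adjusted model. The two can disagree on the same contrast, and the text gives no rule for which decides. If the chi-square p-value is the one reported, an arm could be declared better than usual care, or better than another arm, too often when nothing differs. Bonferroni does not repair this, because it lowers the threshold for p-values that are already too small.

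**Working it through.** **Inputs, all from Sample Size Calculations.** Rates of 30% and 40%; "having a power of 80% with an alpha error at .05" (two-sided is my reading, and it reproduces the plan's number); ICC .05; 15 children per cluster; "The sample size per arm would be 615 per arm or 3075 for all 5 arms".

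**Step 1. Reproduce the plan's sample size.**
- Independent children per arm (unpooled variance): (1.960 + 0.842)² × (0.30×0.70 + 0.40×0.60) / 0.10² = 353.2.
- Design effect: 1 + (15 − 1) × .05 = 1.70.
- 353.2 × 1.70 = 600.4 per arm. Divided by 15 this is just over 40, so 41 clusters, and 41 × 15 = 615 per arm, 1230 for two arms.

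This matches the text and Table 3 exactly. The same formula reproduces four other cells of Table 3 that were checked (810, 1400, 1740 and 1710), so the design effect is built into the plan's own numbers.

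**Step 2. False-positive rate of a test that ignores clustering.** Under no difference, the naive z statistic has variance equal to the design effect (DE) instead of 1. The true error at nominal level α is 2 × [1 − Φ(z₁₋α/₂ / √DE)], with √1.70 = 1.304.

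| Nominal two-sided level | z | z / 1.304 | True error |
|---|---|---|---|
| 5% | 1.960 | 1.503 | 13.3% |
| 1.25% (Bonferroni, 4 tests assumed) | 2.498 | 1.916 | 5.5% |
| 0.5% (Bonferroni, 10 tests assumed) | 2.807 | 2.153 | 3.1% |

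Four is the number of comparisons with control; ten is the number of pairs among five arms (5 × 4 / 2). The document fixes neither.

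**Step 3. Check by simulation.** Beta-binomial data were generated with 41 clusters of 15 per arm, a 30% rate in both arms, ICC .05 and 40,000 replicates. The chi-square test rejected in 13.1% at nominal 5%, 5.5% at 1.25% and 3.1% at 0.5%. A t-test on cluster-level proportions, which respects the clusters, rejected in 5.0% at nominal 5%.

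**Step 4. Sensitivity of the 5% row.**

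| ICC | Cluster size | DE | True error |
|---|---|---|---|
| .01 | 15 | 1.14 | 6.6% |
| .05 | 10 | 1.45 | 10.4% |
| .05 | 15 | 1.70 | 13.3% |
| .05 | 20 | 1.95 | 16.0% |
| .10 | 15 | 2.40 | 20.6% |

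The error exceeds its nominal level in every row; its size depends mainly on the ICC, which is an assumption of the plan.

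**The case against.** The strongest reply is that the problem is recognised and handled in the same paragraph. Shortly after the chi-square sentence, the text gives the correct reason for a cluster-aware analysis and names valid methods, and the sample size is inflated to match. The word first gives an order, not a decision rule, and an unadjusted comparison followed by adjusted models is a common reporting sequence. Which listed model is primary, and the choice between GEE and GLMM, can be left to a full protocol or SAP that is not shown here.

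Much of this stands, and it rules out three stronger readings.

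- A reader might infer that the trial's primary analysis ignores clustering and so has a 13% false-positive rate. The document does not support that. The 13% belongs to the chi-square test and becomes the trial's error only if that test decides, which the text neither states nor excludes.
- A reader might infer that the multivariable logistic regression is also an unclustered analysis. The text does not say so. For a binary outcome, a GEE or GLMM with a logit link is a multivariable logistic regression, and the next sentence can be read as saying how that model is fitted.
- A reader might take 13% as the error at the level the plan would use. With Bonferroni the per-test level is lower, and the relevant figures are nearer 5.5% or 3.1%, depending on an assumed number of tests. They are still inflated, but they are not 13%.

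The reply does not remove the chi-square sentence itself. This is not a detail left unsaid. The article names, for the primary outcome, a test whose variance is wrong for the design, and does not confine it to description.

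**Conclusion.** The concern holds in a limited form. An ordinary chi-square test is the first comparison named for the primary outcome, and on the plan's own ICC and cluster size its true error is about 13% at a nominal 5%. At Bonferroni levels of 1.25% and 0.5% it is about 5.5% and 3.1%. The article also commits to a valid cluster-adjusted model, but does not say that this model governs the arm contrasts.

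The figures assume an ICC of .05, equal clusters of 15, two-sided tests, and families of 4 or 10 comparisons for the Bonferroni rows. They bear on the trial's conclusions only if chi-square p-values are used for inference.

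**What to change.** Amend the paragraph in Analysis of Quantitative Data in two places.

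1. Replace the unadjusted chi-square test with a cluster-adjusted comparison, either a Rao-Scott chi-square test or a test on cluster-level proportions. Alternatively, show the raw percentages by arm descriptively only.
2. State that the multivariable logistic model is fitted either as GEE with cluster-robust variance or as GLMM with a cluster random effect, that this model is the sole source of p-values and confidence intervals for the arm contrasts, and that the Bonferroni correction is applied to those p-values.

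This takes a sentence or two and needs no change to recruitment, data collection or sample size, since 615 per arm already includes the design effect. The price is that p-values will be less favourable than those from the naive test.

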**Methods:**

This is a mixed methods study using a clustered randomized controlled trial with 4 intervention arms and 1 control arm, augmented by qualitative interviews for personalizing the message. The study is being conducted in Pakistan (an urban site in Karachi and a rural site Matiari). In Karachi, 250 administrative structures are taken as 1 cluster, whereas in Matiari, a catchment area of 4 Lady Health Workers is considered as 1 cluster. The intervention targets families to receive weekly 1-way or 2-way (interactive) personalized automated SMS or automated phone call messages regarding vaccination. Possible barriers to vaccination are assessed in each family at the time of inclusion to determine the type of personalized messages that should be sent to the family to increase the chance of a positive response. Finally, in-depth interviews using purposive sampling are conducted before and after the trial to determine the family’s vaccination experience and related factors.

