### Karachi Site

The data for live births and population of each site in Karachi will be obtained from HDSS team. Data will be scrutinized and divided according to 4 sites in the study, with each site consisting of 5 arms (5 clusters). Administrative structures will be assigned to each intervention through stratified (ie, site) randomization.

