### Matiari Site

As Matiari site has not been stratified into clusters according to HDSS, we randomly allocated 30 clusters per arm. The catchment area of 4 LHWs will be considered as 1 cluster. Each intervention arm will then be randomly allocated to 24 administrative structures (clusters; see Figure 5).

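### Clusters are randomised by site, but the cluster-adjusted model names no site term; if coverage differs between sites, that model is conservative and gives up power

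*Protocol article*

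**What the plan says.** The trial runs in two settings, "an urban site in Karachi and a rural site Matiari". For Karachi, which has four sites, the Karachi Site section says: "Administrative structures will be assigned to each intervention through stratified (ie, site) randomization". The Matiari Site section describes a separate allocation: "Each intervention arm will then be randomly allocated to 24 administrative structures" (the same section also gives 30 clusters per arm, and the two counts need reconciling).

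The section Analysis of Quantitative Data lists a chi-square test first. It then says "Multivariable logistic regression analyses will be conducted to adjust for confounders", and goes on to a GLMM or GEE for within-cluster correlation and to hierarchical models whose levels are not given. The confounders are not listed. Site, region and randomisation stratum are not named as model terms anywhere in the article.

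**The concern.** Stratified allocation spreads each site evenly over the arms, so differences in coverage between sites no longer add to the sampling error of the arm comparison. A model gets the benefit only if it knows about the strata. A GLMM or GEE whose only structure is the cluster counts between-site differences as between-cluster variance. Its standard error is then wider than the true sampling variation, its type I error falls below nominal, and power is lost.

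The strata could well matter. By the article's own description they are coastal fishing communities, a dairy area on the edge of Karachi and a rural farming district 185 km away. What is at stake is efficiency. The omission does not bias the comparison or create a false-positive risk in the cluster-adjusted model.

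**Working it through.** **Inputs.** From Sample Size Calculations: "increase in coverage rate from 30% to 40%, having a power of 80% with an alpha error at .05"; "The ICC is taken as .05, with an estimate of 15 NB per cluster"; "The sample size per arm would be 615 per arm or 3075 for all 5 arms". The test is taken as two-sided.

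**The plan's own figure.**
- Individuals per arm: [1.96 × √(2 × .35 × .65) + 0.842 × √(.30 × .70 + .40 × .60)]² / .10² = 356.
- Design effect: 1 + 14 × .05 = 1.70; 356 × 1.70 = 605.2.
- Rounded up to whole clusters: 41 × 15 = 615 per arm, and 82 clusters or 1230 births for two arms. This matches the article exactly.

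**Assumptions added.**
- Two strata, urban and rural. Differences among the four Karachi sites are ignored.
- 24 rural clusters per arm, leaving 41 − 24 = 17 urban.
- A coverage gap d between the strata. The article gives none, so a range is shown.
- ICC .05 within stratum.

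**Formula.** With stratum shares 17/41 and 24/41, the between-stratum variance is B = (17/41)(24/41)d² = .2427d². For an arm with mean coverage p, the within-stratum variance of a cluster proportion is W = [p(1 − p) − B] × 1.70/15.
- True standard error, and the model's when strata are included: √[(W₃₀ + W₄₀)/41].
- Model standard error when strata are left out: √[(W₃₀ + W₄₀ + 2B)/41].

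**At d = 20 points.**
- B = .00971; W₃₀ = .20029 × .1133 = .0227; W₄₀ = .23029 × .1133 = .0261.
- With strata: √(.0488/41) = .0345. Without: √(.0682/41) = .0408, about 18% too wide.
- Power with strata: Φ(.10/.0345 − 1.96) = 83%. Power without: Φ[(.10 − 1.96 × .0408)/.0345] = 72%.

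**At d = 10 points.** B = .00243; the standard errors are .0351 and .0367 (5% too wide); power is 81% with strata and 79% without.

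**Simulation** (beta-binomial, 4000 runs per scenario, cluster-level analysis at .05):

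| Gap d | Power without | Power with | Type I without | Type I with |
|---|---|---|---|---|
| 0 | 80.2% | 80.1% | 5.4% | 5.4% |
| 10 | 77.9% | 80.6% | 4.1% | 5.1% |
| 20 | 69.4% | 81.1% | 1.7% | 4.8% |

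A logistic GEE at d = 20 (400 runs) points the same way: power 70.5% without and 82% with the term, type I error 1.75% without. With the term its type I error was 7.25%. The Monte Carlo standard error is √(.05 × .95/400) = 1.1 points, so some of the 82% may reflect a slightly liberal robust variance rather than the stratum term.

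**If .05 is the total ICC.** The scenarios above add the gap on top of .05. At p = .30 and d = 20 the total ICC would be (.00971 + .05 × .20029)/.21 = .094. Holding the total at .05 instead, simulated power at gaps of 0, 10, 15 and 20 points is 80%, 81%, 83% and 87% without strata, and 80%, 83%, 89% and 95% with them. A repeat with 8000 runs agreed to within about 2 points.

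**Analyses without a cluster term.** In the same simulations the plain chi-square test had a type I error of 14.4%, 13.1% and 12.0% at gaps of 0, 10 and 20 points. Its error runs in the opposite direction.

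**The case against.** The strongest reply is that the article is silent on site and does not exclude it. Unlisted confounders could include site, the hierarchical models could have a site level, and a fuller analysis plan may name it. That stands. A reader might infer that the trial has decided to ignore its strata, and the text does not show that. The point remains worth making because the section does state an adjustment rule, and that rule does not carry through the one factor known in advance from the randomisation.

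A second reply is that the harm is conditional. This also stands: there is no loss at equal coverage, about 3 points of power at a 10-point gap, and the 12-point loss at a 20-point gap needs a total ICC near .09, well above the planned .05. A reader might infer that the trial falls below its planned 80%. That is not established, because the article does not say whether .05 is a total or a within-site value.

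Third, the logistic regression sentence mentions no cluster term, so it cannot by itself produce standard errors that are too wide. That is right; the point applies only to the GLMM/GEE in the sentence that follows it.

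Two further inferences are not supported. The article describes no data-driven choice of confounders; an unlisted set is not evidence of selection. And power after the Bonferroni correction is a separate question: every figure here is at .05.

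**Conclusion.** The point holds as an inexpensive improvement. The design uses site in allocation and the cluster-adjusted analysis does not name it. If coverage differs between strata, that analysis is conservative, with a standard error about 5% too wide at a 10-point gap and about 18% too wide at 20 points. The size rests on assumed gaps, an assumed 17/24 split and an ICC of .05 within stratum. With 30 rural clusters out of 41 the between-stratum factor would be (11/41)(30/41) = .196 instead of .243, so the loss would be somewhat smaller. If .05 is the total ICC, planned power is kept at every gap examined and the term gives extra power. The omission brings neither bias nor an inflated type I error into the GLMM/GEE.

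**What to change.** In Analysis of Quantitative Data, state that the randomisation strata enter the primary GLMM or GEE as fixed effects, with the four Karachi sites and Matiari as the fifth level, and that the Cox model uses the same factor as strata or covariates. Matiari should stay a single level, since the article documents no stratification by area within it. Site is already held for every cluster. The cost is about 4 degrees of freedom among the 5 × 41 = 205 planned clusters, and in the simulation at no gap the term made no material difference to power (80.2% without, 80.1% with).
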